#### Inclusion and exclusion criteria

A total of 60 patients scheduled for ACLR will be recruited. After enrollment, participant information will be entered into the RED Cap system, and participants will be randomly assigned to two groups (experimental group, *n* = 30; control group, *n* = 30) using a mixed block randomization method. This is a single-blind randomized controlled trial; participants will not be informed of their group assignment or the intervention details prior to the intervention. Baseline information and data will be collected preoperatively. After the study procedures have been fully explained and understood, written informed consent will be obtained from all participants at the Department of Sports Medicine, Peking University Third Hospital. All data collection and interventions will be conducted at the same department.

Inclusion Criteria: (1) age 18–35 years; (2) diagnosis of ACL rupture confirmed by MRI; (3) first-time unilateral ACL rupture scheduled for reconstruction at our institution; (4) body mass index (BMI) within the normal range of 18.5–23.9 kg/m^2^ (to exclude the confounding effect of obesity on joint loading); (5) time since injury less than 6 months; (6) affected knee has passed the acute phase, with no significant swelling, pain, inflammation, or range of motion limitation, and basic joint mobility is restored.

Exclusion Criteria: (1) history of musculoskeletal injury or surgery on the contralateral lower limb; (2) time since ACL injury 6 months; (3) cartilage injury with Outerbridge grade III or IV; (4) concurrent meniscal tear requiring meniscal repair during ACLR; (5) concomitant severe injury to the posterior cruciate ligament, medial collateral ligament, or lateral collateral ligament; (6) presence of metabolic syndrome (obesity, dyslipidemia, diabetes, etc.), immune system diseases affecting articular cartilage, or severe cardiovascular or cerebrovascular diseases; (7) unwillingness to receive the allocated treatment.

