**Methods:**

This study is a single-blind, parallel-group randomized controlled trial. A total of 60 participants scheduled for primary unilateral ACLR will be recruited and randomly allocated to either the experimental group (conventional rehabilitation plus gait retraining) or the control group (conventional rehabilitation only). Gait retraining will commence at 3 weeks post-surgery, lasting for 6 weeks with a frequency of 2–3 sessions per week, each lasting 15–20 min. Data will be collected at baseline (pre-intervention) and at 3 months, 6 months, 1 year, and 2 years postoperatively. Assessment will include three-dimensional gait analysis, surface electromyography (sEMG), isokinetic muscle strength testing, functional magnetic resonance imaging (fMRI), Y-balance test, single-leg hop test, the International Knee Documentation Committee (IKDC) subjective knee evaluation form, Lysholm knee score, and Tegner activity scale. The primary outcome measure is the peak knee flexion moment during walking. Secondary outcomes include cartilage T1*ρ*/T2 values, muscle activation patterns, and subjective functional scores. A repeated-measures analysis of variance (ANOVA) will be used to evaluate the intervention effects on the outcome measures.

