### Participants and recruitment

#### Sample size calculation

The primary outcome measure is the peak knee flexion moment during walking, a key biomechanical indicator of cartilage degeneration (21). A significant difference in this measure will be considered statistically meaningful. Based on preliminary results, the mean peak knee flexion moment before training in ACLR patients is 0.20 BW·BH, with a standard deviation of 0.09. After training, the mean peak knee flexion moment is 0.28 BW·BH, with a standard deviation of 0.11 Nm/kg/m. Using the formula for sample size estimation for two independent samples, $n=\frac{2\sigma^{2}{\left(Z_{\alpha /2}+Z_{\beta }\right)}^{2}}{\delta^{2}}$, with *α* = 0.05 and *β* = 0.2,among $\sigma =\sqrt[{2}]{\frac{\sigma_{1}^{2}+\sigma_{2}^{2}}{2}}$, $\delta =\bar{X_{1}}-\bar{X_{2}}$, the required sample size for each group was calculated to be 25.Accounting for a 20% dropout rate, 30 participants per group will be recruited. The required sample size corresponds to a Cohen's d of 0.8, indicating a large effect size.

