### Outcome measures

#### Measurement procedures

Participants will complete baseline information and subjective functional scoring scales (including basic information, IKDC2000 subjective knee function score, Tegner activity level score, Lysholm knee score, pain VAS score, and dominant side questionnaire). Subsequently, bilateral knee MRI (including functional MRI), three-dimensional gait biomechanics, isokinetic muscle strength, and lower limb balance tests will be conducted. All tests will be performed at baseline, 3 months, 6 months, 1 year, and 2 years postoperatively.

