### Statistical analysis

The primary analysis will employ a mixed-effects model to account for within-subject correlations across repeated measures during the 2-year follow-up and to handle potentially missing data at random. All statistical tests will be performed with a significance level set at *α* = 0.05. A repeated-measures two-way analysis of variance (ANOVA) will be used to evaluate the interaction effects between group (experimental vs. control) and time (baseline, 3 months, 6 months, 1 year, and 2 years) on cartilage biochemical characteristics derived from functional MRI (T1*ρ*/T2 values) and on gait parameters. For multiple comparisons, the Bonferroni correction will be applied. For EMG data, repeated-measures ANOVA will be used to assess the differences in muscle activation patterns before and after gait retraining, thereby exploring the neuromuscular control mechanisms underlying the effects of gait retraining on gait biomechanics. To control the false discovery rate (FDR) when comparing MRI parameters across 10 cartilage subregions and multiple time points, the FDR method will be applied with the threshold set at 0.05. Missing data will be assumed to be missing at random (MAR) and will be addressed using the mixed-effects model without imputation or deletion. For the analysis populations, the primary analysis will follow the intention-to-treat (ITT) principle, including all participants as originally randomized. Sensitivity analysis will be performed using a per-protocol (PP) set, including only participants who completed the full intervention and all follow-up assessments. Effect sizes will be reported as partial eta-squared (*η*^2^). Outliers, defined as values exceeding ±3 standard deviations from the group mean, will be excluded and reanalyzed in a sensitivity analysis.

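### Baseline is preoperative and no visit falls between surgery and training, so the EMG before/after comparison cannot isolate the effect of gait retraining

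*Protocol article*

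**What the plan says.** **Timing of baseline.** The protocol article, under Inclusion and exclusion criteria, says: "Baseline information and data will be collected preoperatively". The Methods paragraph of the abstract says: "Data will be collected at baseline (pre-intervention) and at 3 months, 6 months, 1 year, and 2 years postoperatively".

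**Timing of training.** The same abstract paragraph says: "Gait retraining will commence at 3 weeks post-surgery, lasting for 6 weeks". The section on the experimental group also gives 3 weeks after surgery as the start.

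**Visits.** Under Measurement procedures: "All tests will be performed at baseline, 3 months, 6 months, 1 year, and 2 years postoperatively". Study design gives the same five time points, and the time factor under Statistical analysis has the same five levels. The text names no visit after surgery and before training.

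**EMG analysis.** Under Statistical analysis: "repeated-measures ANOVA will be used to assess the differences in muscle activation patterns before and after gait retraining". The stated aim is to explore the neuromuscular mechanisms by which retraining affects gait. The sentence names neither the visits to be compared nor a group term.

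**The concern.** A comparison of muscle activation before and after retraining supports a statement about retraining only if the before value describes the knee as it was when training began, or if a concurrent control group removes whatever else happened in between. With a preoperative baseline the first condition fails: the last measurement before training is on an ACL-deficient knee, and the operation plus 3 weeks of recovery and exercises come before the first training session. The second condition is available in this trial, but the EMG sentence does not invoke it.

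At stake is the mechanistic conclusion. Muscle activation may well change from the preoperative visit to 3 months in both arms. Read as written, a significant time effect in the experimental arm could be reported as evidence of how retraining acts, although surgery and ordinary recovery could have produced it. The abstract's looser label adds to this, because it lets a reader suppose that baseline was taken just before training.

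**Working it through.** No effect size can be computed, because the document gives no EMG values and no preoperative gait values. The check is a timeline, a decomposition of the change, and a check of whether the sample size is touched.

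**1. Timeline (weeks after surgery).**
- Baseline: before week 0 (Inclusion and exclusion criteria).
- Training starts: week 3.
- Training ends: 3 + 6 = week 9.
- First follow-up: 3 months, about week 13.

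The interval from baseline to first follow-up therefore contains the operation, 3 weeks before training, 6 weeks of training and about 13 − 9 = 4 weeks after it. Retraining occupies about 6 of 13 postoperative weeks, and conventional rehabilitation runs throughout.

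**2. What a change from baseline contains.** Write S for the effect of the reconstruction, H for healing over time, C for conventional rehabilitation and R for adding retraining. The expected change from baseline to 3 months is:
- experimental arm: S + H + C + R
- control arm: S + H + C
- difference between arms: R

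The within-arm change in the experimental group equals R only if S + H + C = 0, which nothing in the document supports. The difference between arms gives R because randomisation makes the other terms equal in expectation. R here is the programme as delivered, including the omission of the standard walking exercise on retraining days.

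**3. Which analyses are affected.**
- T1rho/T2 and gait parameters: the plan specifies the interaction of group and time, which is the third line above. Not affected, provided every participant has the same baseline visit.
- EMG: the plan specifies a before/after comparison without naming group, which as written is the first line. Affected.

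**4. Sample size.** Inputs from Sample size calculation: means 0.20 and 0.28, SDs 0.09 and 0.11, two-sided α = 0.05, β = 0.2.
- Pooled SD: √((0.09² + 0.11²)/2) = √0.0101 = 0.1005
- d = 0.08/0.1005 = 0.796, against the stated 0.8
- n = 2 × 0.0101 × (1.960 + 0.842)²/0.08² = 24.77, rounded up to 25 per group, as stated

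The formula takes two means and a pooled SD and has no term for a baseline visit. The timing of baseline does not change the 25.

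**The case against.** The strongest reply is that the timing is not contradictory. The Methods sentence is explicit, a preoperative visit is also before the intervention, and patients are recruited while scheduled for surgery. This stands: the abstract's label is imprecise but compatible. A reader might infer that some baselines will be taken before surgery and some at week 3, but no passage places baseline at week 3. Figure 1, which may show the visits, is not available here.

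A second reply is that both arms undergo surgery, early healing and the same conventional programme, so these cancel in the randomised comparison. This also stands, and is why the primary outcome and the MRI measures are outside the point. It does not rescue the EMG sentence, which describes a before/after difference and not a difference between arms. EMG is recorded during gait analysis, and the authors may intend the same group-by-time model for it, or the full analysis plan may say so. If so, the article's wording should match.

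Three further inferences are tempting but not supported:
- **The sample size is undermined**, because "the mean peak knee flexion moment before training in ACLR patients is 0.20 BW·BH" describes a state that the trial would not measure. The figure is a planning input from preliminary results; a two-sample calculation needs no matching visit in the trial, and the article does not say exactly when the pilot measurement was made.
- **The test battery conflicts with the loading steps in Table 1.** This arises only if baseline is at week 3, which the text does not say. Table 1 describes loading during the treadmill intervention and is not stated as a limit on all weight-bearing.
- **Power is lost through a weakly correlated baseline.** The document gives no correlation between visits, so any such figure would rest on assumption alone.

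**Conclusion.** The point holds in a limited form. With baseline taken preoperatively and no visit between surgery and training, a within-patient EMG change mixes the reconstruction, early healing and conventional rehabilitation with retraining. It cannot support a statement about how retraining works. The abstract's label for baseline should be tightened, but it is an ambiguity and not a contradiction.

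The consequence is a confounded attribution in one secondary, exploratory analysis. Its numerical size cannot be derived from the document. The randomised comparisons of peak knee flexion moment and T1rho/T2, and the 25 per group, are unaffected.

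The conclusion assumes that the Methods sentence governs the timing of baseline, that the figure not shown adds no visit between surgery and training, and that the EMG sentence means what it says.

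**What to change.** 1. In the abstract, replace the pre-intervention label with preoperative. Use the same term in Study design and Measurement procedures, in line with Inclusion and exclusion criteria, and state that this one visit is the baseline for every participant in all models.
2. In Statistical analysis, replace the EMG before/after comparison with the randomised group-by-time contrast: experimental versus control change from the preoperative baseline, over the follow-up visits already listed.
3. Add that within-arm EMG change is descriptive and will not be attributed to retraining.

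The cost is wording in a few places and a group-by-time term of the kind already planned for gait parameters. It needs no new visit, no additional participants and no change to the sample size.

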### Outcome measures

#### Measurement procedures

Participants will complete baseline information and subjective functional scoring scales (including basic information, IKDC2000 subjective knee function score, Tegner activity level score, Lysholm knee score, pain VAS score, and dominant side questionnaire). Subsequently, bilateral knee MRI (including functional MRI), three-dimensional gait biomechanics, isokinetic muscle strength, and lower limb balance tests will be conducted. All tests will be performed at baseline, 3 months, 6 months, 1 year, and 2 years postoperatively.

#### Gait analysis

A 10-camera three-dimensional motion capture system (Vicon) will be used to collect three-dimensional kinematic data during walking at a sampling rate of 100 Hz. Ground reaction forces will be collected synchronously using embedded force plates at a sampling rate of 1,000 Hz. Synchronization between the force plates and the motion capture system will be achieved via a hardware trigger signal. Surface electromyography (EMG) will be used to assess muscle activation levels of the quadriceps, hamstrings, tibialis anterior, and gastrocnemius during walking at a sampling rate of 2,000 Hz. EMG electrodes will be placed according to the SENIAM (Surface ElectroMyoGraphy for the Non-Invasive Assessment of Muscles) recommendations, positioned over the muscle belly and aligned with the muscle fiber direction. Gait biomechanical analysis will be performed using Visual 3D software (C-motion, USA) to calculate three-dimensional kinematics and kinetics of the hip, knee, and ankle joints. Additionally, an Anybody musculoskeletal multibody dynamics model (18 rigid bodies, 92 muscles) will be used to calculate overall knee joint contact forces, anterior-posterior and shear forces, and individual muscle forces using inverse dynamics.

### Basic motor function tests

#### Isokinetic muscle strength test

Isokinetic strength of the knee extensors and flexors will be assessed using a dynamometer (Con-Trex MJ, Fitzmann, Germany). Participants will be securely strapped at the trunk and thigh. The knee will be moved from 90° to 20° flexion (and back) at angular velocities of 60 °/s, 180 °/s, and 300 °/s for concentric and eccentric contractions, following standardized protocols.

#### Y-balance test

Participants will stand on a single leg with the great toe aligned with the starting line on the testing platform. The other foot will be used to push the testing board as far as possible in the anterior, posteromedial, and posterolateral directions. The farthest distance reached (accurate to 0.5 cm) will be recorded for each direction, with three repetitions.

#### Single-leg hop test (to be performed at 6 months, 1 year, and 2 years post-surgery)

This includes the single-leg hop, triple single-leg hop, diagonal triple single-leg hop, and 6-meter timed hop. Two formal tests will be performed per participant, and the best result will be recorded. A rest interval of 30 s will be provided between tests.

### Lysholm knee score

Lysholm is a quantitative score for daily symptoms and exercise capacity of the knee joint. This scoring system contains eight questions. The total score ranges from 0 to 100, with higher scores indicating better knee function. According to the score results, the functional status of the knee joint of the patient can be evaluated. More than 95 points are excellent, 94–85 points are good, 84–65 points are fair, and less than 65 points are poor (22).

### IKDC 2,000 subjective knee score

IKDC 2000 knee subjective rating scale is a widely used tool to evaluate knee function and symptoms, especially for patients after knee injury or surgery (23).The scale assesses the performance of the knee joint in daily activities through patient self-report. The overall score ranges from 0 to 100, with higher scores indicating better knee function.

### Tegner activity level score

The Tegner rating scale is a tool commonly used to assess the degree of athletic injury and functional recovery to assess the ability to perform athletic activities after knee injury. The Tegner rating scale is graded on a scale from 0 to 10 based on the level of motor activity participants engage in and the gradual increase in demands (24).

### Functional MRI

Early cartilage degeneration may not be detectable on conventional MRI due to the absence of morphological changes; therefore, functional MRI techniques will be used to assess cartilage relaxation times. A GE 750 W 3.0 T MRI scanner will be used to scan bilateral knees. The protocol includes T1*ρ* and T2 mapping sequences, which reflect cartilage biochemical characteristics (collagen and proteoglycan content). Increases in these values indicate a time-dependent decline in collagen and proteoglycan content, signifying early cartilage degeneration (25–27).The T2 mapping sequence will be performed using a 3D multi-echo fast spin-echo sequence (TR/TE = 9.3/3.7 ms, echo train length = 8). The T1*ρ* sequence will use a spin-lock pulse (locking frequency = 500 Hz, locking time = 10 ms). Other parameters include: FOV = 16 cm, matrix = 256 × 256, slice thickness = 1 mm, voxel size = 0.625 × 0.625 × 1 mm^3^, number of slices = 32, and fat suppression technique (SPECIAL). The regions of analysis will include the medial and lateral femoral condyles, femoral trochlea, medial and lateral tibial plateaus, and patellar cartilage, as illustrated in Figure 2.

**Figure 2 F2:**
[figure not shown]
Schematic representation of cartilage partitions in the knee joint. AI segmentation + manual fine tuning in 21 zones of knee cartilage and VR segmentation effect.

### Postoperative gait intervention

#### Experimental group

Participants in the experimental group will undergo standard postoperative rehabilitation as outlined below. In addition, starting from 3 weeks post-surgery, they will concurrently receive a 6-week gait retraining program using a lower-body positive pressure (LBPP) system (Anti-Gravity Treadmill, AlterG). On days when the gait retraining intervention is performed, the walking training component of the standard postoperative rehabilitation protocol will be omitted. After the gait retraining session, patients will continue with their home-based rehabilitation as per the standard protocol.

The anti-gravity treadmill (AlterG) comprises a lower-body positive pressure (LBPP) chamber and a visual feedback screen. During walking, pneumatic pressure unloads a percentage of body weight, thereby reducing knee joint loading and potentially alleviating pain. The LBPP treadmill has been shown to reduce knee pain in patients with knee osteoarthritis (28). It provides a relatively safe environment for walking, offering advantages over traditional therapy for the restoration of walking ability, gait correction, and balance improvement (28–30). It integrates the three key elements of walking—loading, stepping, and balance—thereby facilitating the formation of normal gait patterns (29, 31).

The intervention will begin at 3 weeks post-surgery, with sessions conducted 3 times per week for 6 weeks. Each session will last 15–30 min (3 sets × 5–10 min/day, with 90-s rest intervals between sets). Each session will include a 5-min warm-up, followed by 5–10 min of stretching and ice application post-training. During the gait retraining, lower limb orthoses will be removed. Lower limb weight-bearing will be quantitatively and individually adjusted based on the postoperative week and the participant's condition (Table 1). During the gait retraining, the LBPP system's interactive screen will provide real-time feedback on bilateral lower limb weight-bearing and gait posture. The screen will display metrics such as ground reaction force on both feet, stance time, walking speed, step length, and steps per minute. Participants will be instructed to self-adjust their weight-bearing and gait patterns in real-time, using the visual feedback to achieve symmetry between limbs in ground reaction forces, step length, and stance time, with the goal of balanced bilateral weight-bearing throughout the gait cycle (Figure 3).

**Table 1 T1:** Gait intervention protocol after ACLR.

Content	The first week	The second week	The third week	The fourth week	The fifth week	The sixth week
Loading degree	30%body weight	50%body weight	65%body weight	80%body weight	100%body weight	100%body weight
Time/time	15 min (3 × 5 min)	15 min (3 × 5 min)	15 min (3 × 5 min)	15 min (3 × 5 min)	1 (3 × 5 min)	15 min (3 × 5 min)
Rest/min	90 s	90 s	90 s	90 s	90 s	90 s
Trequency	3 times/week	3 times/week	3 times/week	3 times/week	3 times/week	3 times/week
Speed	Optional comfort speed (does not cause or aggravate pain)					

**Figure 3 F3:**
[figure not shown]
Gait training combined with weight loss and visual feedback.

Stop Criteria:** The intervention will be terminated if the visual analog scale (VAS) pain score exceeds 4 points during a session, or if knee joint swelling increases by more than 10% compared to pre-session levels. VAS pain scores will be assessed before, during (at rest intervals), and immediately after gait retraining. Knee joint swelling will be assessed before and immediately after gait retraining.

